## Abstract

**Background:**

Despite the comparatively high prevalence of possible sarcopenia among young-old adults in the community, there is currently no available and effective social media-based intervention to increase the awareness and change the behavior of the target population to prevent sarcopenia. Using co-design methodology, we developed a multicomponent intervention strategy of health education and exercise for sarcopenia prevention utilizing the TikTok platform.

**Objectives:**

The primary purpose of this study is to examine the feasibility and acceptability of the social media-based intervention to enhance muscle function in community-dwelling young-old adults with possible sarcopenia.

**Methods:**

This protocol outlines the entire research procedure for a prospective single-arm pre-post feasibility study employing a mixed-method design, which will be conducted between May 2024 and September 2024. Thirty-five older adults aged 60–69 years with possible sarcopenia will be recruited from two communities in Changsha, China. Using the TikTok platform, participants will be required to view a total of seven health education videos in the first week, and each video lasts four to six minutes. Then, participants will receive six-week multi-component exercise through TikTok, with at least three sessions/week, 30 minutes/session, and moderate intensity. Data collection will be conducted in baseline, week 1, 4, 7, 10 and 13. The primary outcomes will include evaluating recruitment capability, data collection procedure, outcome measurement, intervention procedures’ acceptability, researchers’ ability to manage and implement the study, among others. The secondary outcome is to compare standard measures for muscle function (e.g. handgrip strength, skeletal muscle mass, physical performance), body composition (e.g. body fat, body mass index, bone mineral), and other measures (e.g. perceived knowledge, personal motivation, behavioral skills). Finally, all participants will be offered a semi-structured interview to assess their in-depth experiences with the intervention and research process.

**Discussion:**

This study will be the first social-media based multicomponent intervention program for community young-old adults with possible sarcopenia to improve their muscle function, awareness and behavior of preventing sarcopenia. Findings will generate new evidence regarding the use of social media in health education for improving awareness of sarcopenia prevention, as well as the feasibility of using social media to influence participants’ behavioral changes through exercise. This may help researchers identify ways to optimize acceptability and efficacy of the SHEEP intervention for the targeted population.

**Trial registration:**

ISRCTN registry, ISRCTN17269170, Registered 14 September 2023.

## Introduction

Possible or probable sarcopenia is defined as age-related low muscle strength, with or without reduced physical performance [1,2]. It is highly prevalent among older adults in the community according to ample evidence [3–7]. Several factors such as increased age [5–9], male gender [5,10], living in rural areas [7], having other disease conditions (e.g., diabetes, hypertension, chronic lung diseases, chronic kidney disease, heart disease, arthritis, osteoarthritis, osteoporosis, rheumatism, frailty, malnutrition, depression and psychiatric conditions) [4–7,9–11], physical inactivity [4–6,8,9], and having a history of falls [7] were associated with higher prevalence of possible sarcopenia. Moreover, receiving a higher level of education is associated with a lower risk of possible sarcopenia [6]. It is notable that some factors associated with this condition are preventable, treatable, and modifiable. Hence, the authoritative international associations for sarcopenia prevention recommend possible sarcopenia as a significant threshold in medical practice to trigger assessment of causes and initiate intervention [1,2].

There are a limited number of interventions specifically designed to prevent possible sarcopenia in community-dwelling young-old adults. Our previous scoping review indicated that most studies of sarcopenia interventions recruited participants older than 70 years, while young-old adults aged 60–69 years received less attention [12]. For example, Merchant et al. [13] discovered that community-based dual-task exercise could improve handgrip strength, physical performance, perceived health, cognition, and reduce falls and frailty in Singaporean older adults (mean age 75.9y) with possible sarcopenia. Jones et al. [14] conducted a one-group, pre-post experimental study to examine the Healthy Beat Acupunch (non-invasive punching movements based on traditional Chinese medicine) exercise program on sarcopenia prevention and found that it was simple, safe, appropriate, and beneficial for practice by Australian older adults (mean age 81.2y) with probable sarcopenia and could improve participants’ gait speed. Another recent Taiwanese study examined the impacts of vitality acupunch exercise on older adults (mean age 80.5y) with possible sarcopenia, concluding that acupunch exercise has positive effects on the muscle mass, hand grip strength, and sleep quality of participants after a six-month intervention [15]. Furthermore, Pan et al. [16] designed a multicomponent intervention strategy consisting of nutrition, resistance exercise, and health education for community- dwelling Chinese seniors (mean age 71.6y) with possible sarcopenia, which increased their muscle mass and handgrip strength and decreased the duration of the timed up-and-go test and the five-times chair stand test. Additionally, the proportion of non-pharmaceutical interventions for older individuals with possible sarcopenia (11.9%) was substantially lower than that for sarcopenia (72.9%) in the community [12].

Meanwhile, our recently published scoping review revealed a paucity of research exploring the intervention type of ‘health education plus exercise’ in sarcopenia prevention [12]. While exercise is a widely recognized non-pharmacological strategy for managing sarcopenia [1,2], the effectiveness of health education remains ambiguous due to its relatively limited focus in this domain [3,12]. Our scoping review showed that the total number of health education interventions (15.5%) is small when compared with exercise (52.8%) or nutrition interventions (34.5%) to prevent possible sarcopenia or sarcopenia in the community [12]. Our review also indicated that more than 80% of the educational materials promoted in health education interventions were not explicitly related to sarcopenia [12]. This may be the primary cause for the unsatisfactory outcomes of current health education for sarcopenia prevention [3,12]. In addition, the identified intervention methods for delivering health education to prevent possible sarcopenia or sarcopenia were traditional, including group-based classes, face-to-face interactions and printed leaflets/materials [12].

Social media has become a promising platform for health education and behavior change in prevention of diseases in recent years, but there are no reports in the sarcopenic area. For instance, a recent study demonstrated that participation in a Twitter social media support group for breast cancer patients (of which 32.9% were between 55~74 years) increased overall breast cancer knowledge and decreased anxiety [17]. Another study determined that a video clip followed by a text post was the most effective method of informing hypertensive individuals about the primary prevention of cardiovascular diseases using the Instagram social media platform [18]. Facebook advertising has also been shown to be effective for disseminating hypertension knowledge to older adults in research; with the click‐through rates for older (65 years or older) Chinese Americans higher than those for younger (45‐54 years), at 15% versus 4% respectively [19]. In addition to knowledge dissemination, social media-based interventions are widely used in the promotion of positive behavior change. A national web-based cross-sectional survey in China reported that social media, including TikTok, WeChat and Weibo, was an effective tool to disseminate pandemic news and disease knowledge, and was also beneficial for promoting behaviors to prevent COVID-19 among the public [20]. A systematic review focusing on behavior change interventions through social media found that a majority of studies reported positive outcomes and most of the studies targeted either physical activity or a combination of behaviors that included physical activity (e.g., physical activity, diet and nutrition, and weight loss or weight maintenance) [21]. Moreover, a rapid evidence-based review revealed that studies using social media in interventions have mostly showed superior results to more traditional methods and suggest that public health institutions, clinicians, and other stakeholders consider the use of social media in their interventions targeting people affected with chronic disease [22].

Therefore, our research team co-created a Social-media based Health Education plus Exercise Program (SHEEP) for preventing possible sarcopenia through behavior change in community-dwelling young-old adults. Full details of the development study are published elsewhere [3,23]. In brief, we constructed a SHEEP Conceptual Model primarily guided by the Behavior Change Wheel (BCW) [24] and the conceptual model for Lifestyle-integrated Functional Exercise using smartphones and smartwatches (eLiFE) [25], with the objective of developing intervention content and the monitoring process. Then, we co-designed a multicomponent social media-based (TikTok) intervention based on the SHEEP Conceptual Model. After a three-week preliminary test, the results from semi-structured interviews indicated that the participants complied well with the SHEEP intervention and provided positive feedback for both health education and exercise components. Not only did participants subjectively report that their grip and leg strength increased after exercise, they perceived that their mood, sleep, and diet also improved. Simultaneously, participants reported that the program positively altered their attitudes and behaviors toward sarcopenia prevention, and that they would continue to exercise after the study was completed. They were also willing to recommend the program to others. To ensure a more impartial assessment of the potential impact of SHEEP intervention on the intended population, we devised this extended feasibility study prior to proceeding with a prospective RCT.

### Study aims and objectives

The main aim of this study is to assess the feasibility and acceptability of the SHEEP intervention to improve muscle function among young-old adults with possible sarcopenia in the community. According to the feasibility checklist created by Orsmond and Cohn [26], the specific objectives of this research are: 1) to assess recruitment capability and sample characteristics; 2) to assess data collection procedures and outcome measurements; 3) to assess intervention and study procedures’ acceptability and suitability; 4) to assess resources and the ability to manage and implement the study and intervention; and 5) to assess participant responsiveness to intervention.

## Materials and methods

### Study design

A single-arm prospective pre-post study will be conducted to evaluate the feasibility, acceptability, and preliminary impact of the SHEEP on the prevention of possible sarcopenia in community-dwelling young-old adults. In this seven-week intervention with six-week follow-up study, both quantitative and qualitative methods will be employed to evaluate the outcomes. This research protocol was based on the Standard Protocol Items: Recommendations for Interventional Trials—13 (SPIRIT-13) checklists (S1 and S2 Files) and Template for Intervention Description and Replication (TIDieR) checklist (S3 File).

### Study setting

This feasibility study will be conducted in Changsha, Hunan Province, China, with the assistance of our Chinese collaborators. The recruitment and intervention procedure will be carried out in two communities, including Sanchaji Community Health Service Centre and Guanshaling Community Health Service Centre.

### Eligibility criteria

Different scholars have different interpretations of the definition of young-old, like 60–69 or 65–74 [27,28]. Due to a lack of research in the 60–69 year age group (as evidenced from our scoping review [12]) and considering this feasibility study will be carried out in China where ages 60+ are considered an older person [29–31], 60–69 years old is defined as young-old in this study. Trained health professionals and the principal investigator (PI) will approach older adults to take part in this study and they will use the inclusion and exclusion criteria to ensure that only eligible people take part. The following inclusion and exclusion criteria will be considered for the recruitment of participants:

#### · *Inclusion criteria*

60~69 years oldChinese residents living in the communityHave a smart phone with an internet connection at home, existing users of TikTok or have a willingness to download and use TikTok

Individuals with sarcopenia screening questionnaire: Five-item (strength, walking assistance, rising from a chair, stair-climbing, and falls) combined with calf circumference [SARC-CalF] ≥11 [2,32]

Individuals with possible sarcopenia, as defined by low Grip Strength [M:<28 kg, F:<18kg] in accordance with the 2019 Asian working group consensus on diagnosis criteria for sarcopenia [2]Be able to attend the community health center (at their own expense if travel is required) on six occasions for the duration of the studyInformed consent for screening and research

#### · *Exclusion criteria*

Unable to communicate or independently complete learning and exercise using TikTokSerious or unstable medical illness, such as severe cardiovascular or respiratory conditions, mental disorder, dementia, etc.Currently undertaking regular exercise (e.g. Tai Chi and Square Dance) and exercise intensity is moderate (≥ 150mins/week)Contraindications for the use of Bioelectrical Impedance Analysis (BIA), such as people with implanted cardiac pacemakers, or other electronic devices or metal grafts, or with significant pitting oedema, or with limb dysfunction or body paralysis, or while taking medications that affect body composition, such as diuretics or glucocorticoids.

### Recruitment, consent and withdrawal

The PI will visit the two community health centers to present this research to managers and get the approval of the managers. Then, the managers will assist the PI to distribute paper information leaflets to older people who visit community health centers and send electronic information leaflets to community WeChat groups. If older adults are interested in this study after reviewing the leaflet, they can contact the PI through the managers or directly via the contact information listed on the leaflet. To reduce the risk of participants coming to meet with the PI unnecessarily, the PI will conduct a preliminary eligibility screening over phone/email (e.g. confirm items 1–3 and 6 on eligibility list, and exclusion criteria). If confirmed, the PI will invite the participants to meet with them in an office provided by the community health center to tell them more about the study and determine whether they are eligible based on items 4 and 5 (SARC-CalF and grip strength). Potential participants who meet the eligibility requirements will be provided with a full explanation of research that informs them of the detailed research content, the confidentiality of personal information, the potential benefits, the potential risks, and a coping strategy for the risks, should they wish to know. A Participant Information Sheet will be provided for subjects who are still interested and willing to participate in the study, and time will be allowed for consideration (at least 24 hours). Finally, those who agree to participate in the study will be required to provide (written or verbal) informed consent (face-to-face or through phone calls) prior to data collection. If participants choose verbal consent, the PI will read each statement of the consent form and request their response via a dedicated mobile phone. Verbal consent will be separately recorded and stored.

### Research ethics

This study has been approved by the University of Manchester Research Ethics Committee (Project ID: 2024-19302-34066), and permissions have already been granted by collaborators in the Community Nursing Department of Xiang Ya Nursing School, Central South University, China. Amendments to the protocol, study design or supporting documents will be approved by the University of Manchester Research Ethics Committee prior to implementation. All documents will be maintained with version number and tracked changes.

### Sample size

One arm of 35 eligible participants will be recruited. A sample size of 30 participants after attrition (attrition rate 10%~15%) is normally used for a feasibility study [33,34]. Convenience sampling will be utilized in this research. The target population in the two communities will be divided into four categories based on age (60–65 and 66–69 years) and gender (male and female), to determine if there are differences in the acceptability of the intervention process among subgroups of individuals.

### Randomization, allocation, and blinding

This study is a one-arm pre-post feasibility study, so randomization and allocation are not required currently. A cluster RCT is planned, so there is no need to evaluate the feasibility of individual randomization. Blinding is not appropriate for this study as there is only one arm, and the intervention contents include health education, which explicitly specifies that this is a course aimed at the prevention of sarcopenia. Therefore, it can be readily distinguished that the exercise strategy in our study is for muscle health and sarcopenia prevention by researchers and participants when the intervention begins.

### Intervention

Participants will receive the SHEEP intervention strategy [23], which consists of one-week of health education and six-weeks of exercise. Participants will be required to view a total of seven health education videos posted on TikTok in the first week, including the following: 1) What is sarcopenia? 2) What are the common influencing factors in sarcopenia? 3) What are the adverse effects of sarcopenia? 4) What are the manifestations of sarcopenia in daily life? 5) What are the common screening methods for sarcopenia? 6) What are the exercise methods to prevent sarcopenia? 7) What are the nutritional methods to improve sarcopenia? Each video lasts four to six minutes. There is no restriction on the number of views, so participants are allowed to determine the number of videos they watch per day.

Participants will attend a six-week exercise training course on TikTok following completion of the health education learning. The duration of the exercise is fixed at 30 minutes and comprises four types of exercise: 3-minute warm-up training, 8-minute aerobic training, 16-minute resistance training, and 3-minute flexibility training. The multicomponent exercise training is informed by the evidence-based FaME exercise program (https://laterlifetraining.co.uk/real-life-implementation-of-fame-does-it-work /), OTAGO exercise program (https://www.livestronger.org.nz/assets/Uploads/acc116 2-otago-exercise-manual.pdf), and our previous study on intervention development which involved collaboration from stakeholders (physicians, nurses, physiotherapists, older participants) [23]. The training is delivered through pre-recorded videos on TikTok. The frequency of exercise must be at least 3 times/week, and participants can increase the frequency of training per week based on their own preferences. The overall exercise intensity is moderate. The resistance exercise is performed using two 500ml or 1000ml or 1500ml or 2000ml capacity water-bottles. Participants can start from 500ml or 1000ml, then adding 100-500ml of weight every three weeks. The increase in weight is not fixed and can be adjusted according to preference. When the body feels no burden after completing an exercise session, for instance the body does not heat, sweat or muscles do not appear slightly sore after exercise, we suggest appropriately increasing the weight. These water bottles are all made of plastic. 500ml and 1000ml water bottles are more common in mineral water bottles or juice bottles, while 1500ml and 2000ml water bottles are more common in sports water bottles.

Finally, participants will be followed up weekly over another 6 weeks of exercise. The researcher will help them record their exercise diary and feeling through a short telephone call or text message each week.

### Outcomes

As this is a small feasibility study, the main aim is to assess the feasibility and acceptability of the entire research process, from recruitment to the delivery of the intervention and the use of the outcome measurements. The secondary objectives are to compare standard measures at baseline, seven-week post-intervention, and six-week follow-up for muscle-related outcomes, other body measurements as detailed below, and study adherence to evaluate the potential efficacy of the intervention. The outcome measures will be collected at different time points to identify an appropriate primary outcome and estimate parameters for a sample size calculation for an RCT in the future. Final semi-structured interviews with all participants will be conducted to investigate the viability of the intervention and study procedures in greater detail.

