#### · *Secondary outcomes*

Table 1 outlines the two types of secondary outcomes that will be evaluated at various points throughout the study. The first category consists of muscle-related outcomes, including muscle strength, muscle mass, and physical performance. The second category includes additional body parameters such as anthropometric indices, nutrition state, perceived knowledge, personal motivation, behavioral skills, and monitoring of behavior change. The questionnaire survey, like MNA-SF, SEMCD-6, and the Self-Management for Chronic Disease Scale, will be conducted after the physical measurements are assessed. The PI will ask participants the questionnaire questions verbally and will record their answers electronically. If participants wish to see the questionnaires, they will be provided with a paper copy. Those measurements will take about 30–40 minutes in total to complete, which will be assessed in an office provided by the community health center.

**Table 1 pone.0303481.t001:** Overview of instruments and time of outcome measures.

MEASURES	INSTRUMENTS	TIMEPOINT					
		T_0_	Intervention			Follow-up	
			T_1_	T_4_	T_7_	T_10_	T_13_
Social-demographic information	Demographics questionnaire (Self-developed)	**X**					

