**Secondary outcome**							
Handgrip strength	Digital hand-held dynamometer	**X**		**X**	**X**	**X**	**X**
Anthropometric measurements (e.g. weight, height)	Stadiometer + Scale + Plastic tape	**X**		**X**	**X**	**X**	**X**
Body composition (e.g. muscle mass, body fat)	Bioelectrical impedance analyzer device	**X**		**X**	**X**	**X**	**X**
Physical performance	4-Meter Walk Test	**X**		**X**	**X**	**X**	**X**
	Five Times Sit to Stand Test	**X**		**X**	**X**	**X**	**X**
Nutrition state	Mini-Nutritional Assessment Short Form	**X**		**X**	**X**	**X**	**X**
Perceived knowledge	21 true or false quizzes related to sarcopenia (Self-developed)	**X**	**X**	**X**	**X**	**X**	**X**
Personal motivation	Self-efficacy for Managing Chronic Disease 6-item Scale	**X**		**X**	**X**	**X**	**X**
Behavioral skills	Self-management Behavior for Chronic Disease Scale	**X**		**X**	**X**	**X**	**X**
Behavior change monitoring	Exercise diary (Self-developed)	**X**	**X**	**X**	**X**	**X**	**X**
	Exercise Adherence Rating Scale (EARS)	**X**		**X**	**X**	**X**	**X**
	Records of sharing sarcopenia-related information (Self-developed)	**X**	**X**	**X**	**X**	**X**	**X**
	Willingness to formulate habits of regular exercise after study (Self-developed)						**X**
	Records of exposure percentage of exercise and sarcopenia related videos (Self-developed)	**X**	**X**	**X**	**X**	**X**	**X**

Note: T_0_ = baseline; T_1_ = week 1; T_4_ = week 4; T_7_ = week 7; T_10_ = week 10; T_13_ = week 13.

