### Data collection and analysis

The PI, who is qualified and experienced with all of the measurements, will be responsible for data collection. To promote the collection of high-quality data, the PI will double-check the collected data.

As for quantitative data analysis, descriptive statistics will be utilized to summarize the percentage of recruitment, baseline participant characteristics (e.g. age, gender, and educational background), attrition rate, compliance rate, height, weight, etc. 95% confidence intervals (CIs) of mean values will be used to determine the difference of secondary outcomes before and after intervention, such as handgrip strength, skeletal muscle mass, body fat, etc. All statistical analyses will be conducted using SPSS Statistics 27.0 (IBM Corp., Armonk, NY, USA). P Values <0.05 will be interpreted as indicating significance.

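### The efficacy comparison names baseline, week 7 and week 13 only, so week-4 and week-10 readings have no stated part in the change estimates, which can bias them if early response affects dropout

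*Protocol article*

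**What the plan says.** In the protocol article, the Outcomes section names the time points of the efficacy comparison: "The secondary objectives are to compare standard measures at baseline, seven-week post-intervention, and six-week follow-up for muscle-related outcomes". In the notation of Table 1 these are T0, T7 and T13.

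The section on data collection and analysis gives the only stated method for these outcomes: "95% confidence intervals (CIs) of mean values will be used to determine the difference of secondary outcomes before and after intervention". It adds: "P Values <0.05 will be interpreted as indicating significance".

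The measurement schedule is wider. The abstract says: "Data collection will be conducted in baseline, week 1, 4, 7, 10 and 13". Table 1 (note: "T_4_ = week 4; T_7_ = week 7; T_10_ = week 10") marks grip strength, anthropometry, body composition, both physical performance tests, nutrition, knowledge, self-efficacy and self-management at T0, T4, T7, T10 and T13. No comparison in the article names T4 or T10.

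The Outcomes section does give the repeated measurements another purpose: "The outcome measures will be collected at different time points to identify an appropriate primary outcome and estimate parameters for a sample size calculation". The Sample size section plans 35 recruits and 30 remaining after attrition of 10-15%.

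**The concern.** A change from baseline to T7, or to T13, needs a reading at the later visit. Someone measured at T0 and T4 who then leaves supplies no such change, although the T4 reading shows how that person was doing. Computing changes within person does not help, because the later reading is still missing.

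If people who do poorly by week 4 are likelier to leave, the later mean changes describe a selected group and are too favourable. If those who do well leave, the changes are too unfavourable. The article means to use its outcome data to choose a primary outcome and planning parameters for a later randomised trial, so a selected estimate could carry over into that trial's design. The readings that would largely correct this are already scheduled.

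**Working it through.** **1. Visits scheduled against visits compared.** The full battery is scheduled at T0, T4, T7, T10 and T13 (Table 1). The comparison names T0, T7 and T13 (Outcomes). Two of five batteries have no stated role in the change estimates.

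**2. The plan's own figure.** Recruits needed to keep 30:
- 10% attrition: 30/0.90 = 33.3, so 34
- 12.5%: 30/0.875 = 34.3, so 35
- 15%: 30/0.85 = 35.3, so 36

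The stated 35 fits. Expected leavers are 35 × 0.10 = 3.5 to 35 × 0.15 = 5.25. At most this many are affected, since some may leave before T4 or after T7.

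**3. Bias in general form.** The article gives no standard deviation, correlation or dropout mechanism, so these are assumed ranges. With d the fraction leaving and Δ the amount by which stayers' mean change exceeds leavers' (in SD of change), the bias of the completers' mean is d × Δ.

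| Δ | d = 0.10 | d = 0.15 |
|---|---|---|
| 0.25 | 0.025 | 0.0375 |
| 0.5 | 0.05 | 0.075 |
| 1.0 | 0.10 | 0.15 |

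The standard error with 30 completers is 1/√30 = 0.183 SD, so every entry is below one standard error. If leavers are the better responders, Δ and the bias are negative.

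**4. An illustration in kg of grip strength.** Assumed: 35 participants, between-person SD 4 kg, independent visit error SD 1.5 kg, the same true gain for everyone (1.0 kg at T4, 1.5 kg from T7 on), and all dropout after T4.
- SD of an observed change: √(2 × 1.5²) = 2.12 kg
- Correlation of the T4 and T7 changes, through the shared baseline reading: 1.5²/(2 × 1.5²) = 0.5
- Standard error with 30 completers: 2.12/√30 = 0.39 kg

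With logistic dropout on the observed T4 change, slope 1 per SD, the large-sample bias at correlation 0.5 is 0.046 SD (10% dropout) and 0.067 SD (15%). In kg these are 0.046 × 2.12 = 0.10 and 0.067 × 2.12 = 0.14, so completers average 1.60 and 1.64 kg. Simulated studies of 35 agree:

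| Slope per SD | Completers, 10% | Completers, 15% |
|---|---|---|
| 0.5 | 1.54 | 1.56 |
| 1 | 1.61 | 1.65 |
| 2 to 4 | 1.66-1.70 | 1.68-1.75 |

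A further set of simulations gave 1.60-1.73 kg, which is 0.10/1.5 = 7% to 0.23/1.5 = 15% too high, or 0.10/0.39 = 0.3 to 0.23/0.39 = 0.6 standard errors. Weak dependence (slope 0.5) gives 3-4%.

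**5. A ceiling.** If the worst 10% or 15% on T4 change left with certainty, the bias would be 0.5 × 2.12 × φ(z)/(1 − d), with φ the normal density and z the cut-off. For 10% this is 1.06 × 0.1755/0.90 = 0.21, giving 1.71 kg (+14%). For 15% it is 1.06 × 0.233/0.85 = 0.29, giving 1.79 kg (+19%).

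**6. What the extra visits recover.** In the simulated studies, a likelihood model on T0, T7 and T13 alone stayed biased (1.54-1.72 kg). The same model on all five visits gave 1.47-1.52 kg. In large samples, with T4/T7 correlation 0.3-0.9 and slopes 0.5-1.0, completers were biased by 0.02-0.12 SD and an estimator using T4 by about 0. With unrelated dropout all estimators are unbiased, and the all-visit model's standard error is only 1-3% smaller.

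**The case against.** The strongest objection is that naming the time points of a contrast does not fix the estimator. A repeated-measures model could use T4 and T10 and still report exactly the contrasts in the Outcomes section. The article states no completers-only analysis set and no missing-data rule, and such details commonly sit in an analysis plan that is not shown. This stands: a reader might infer that the week-4 readings of early leavers are discarded, and the documents do not say so. What remains is that the two stated elements, three named visits and mean before/after differences, read plainly, give those readings no role.

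A reader might also infer that the reported change is biased toward people who respond well. The documents give no dropout mechanism. The primary aims treat reasons for dropping out as something to be learned, and people who withdraw are offered an interview. Only a conditional statement is justified. In the kg illustration, moreover, everyone has the same true gain, so the bias arises wholly through shared baseline measurement error and does not show a selection of true responders.

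Nor are the T4 and T10 visits wasted. The article says of the battery: "Those measurements will take about 30–40 minutes in total to complete". Two visits for 35 people therefore take 2 × 35 × 30/60 = 35 to 2 × 35 × 40/60 = 47 hours. But participants' burden is itself a feasibility outcome, and repeated measurement is meant to inform the later trial.

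**Conclusion.** The point holds in a limited, conditional form. The stated comparison uses three of the five visits at which the outcomes are measured. Taken as a plain before/after comparison, it loses what early leavers contributed at week 4. This matters only if leaving is related to early response, and the sign depends on why people leave.

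Under the assumed inputs, with poorer early change making dropout likelier, the overstatement is roughly 7-15% of a 1.5 kg gain. An overstatement of a fifth or more is not supported, because even certain dropout of the worst 15% gives 19%. The bias is below one standard error throughout, so it would rarely alter the reading of this study alone. Its relevance is to planning: required size varies with 1/effect², so if a change overstated by 10% were taken as the effect, the size would be too small by 1 − 1/1.10² = 17%. The article does not say that the change will be used that way.

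This is a minor improvement, since feasibility and acceptability are primary and efficacy is secondary.

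**What to change.** State what weeks 4 and 10 contribute to the change estimates. For each continuous secondary outcome measured at all five visits, fit one linear mixed model with visit (T0, T4, T7, T10, T13) as a categorical factor and within-person correlation, using all available readings from every enrolled participant. Report the T7-T0 and T13-T0 contrasts with 95% confidence intervals from that model, which keeps the comparison named in the Outcomes section. Show the completers' paired change beside it as a check. A clear difference between the two would suggest that leavers differed from stayers.

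The model protects against dropout that depends on recorded readings, but not against dropout that depends on what was never measured, so the dropout reasons already being collected should be reported alongside. The cost is a few sentences and slightly more analysis work in the SPSS package already named. No new visits or data are needed.
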